### Pilot study

A one-month pilot study was conducted to assess the feasibility and acceptance of the main study, gathering information which might be helpful for to improve the intervention design. Participants for the pilot study were recruited from the 5 community health centers in Jiading district. Using convenience sampling, 50 eligible patients (27 women and 23 men, mean age 62 years) were recruited in October 2018. Twenty-four of them (15 women and 9 men) and their family members agreed to participate in the pilot study. Patients were randomly and equally divided into intervention and control groups, with 12 in each group. Patients’ family members in the intervention group were invited to subscribe to the WeChat public account *Jiading Sugar Steward* for one month. Limited by time, we were unable to release all of our information via the WeChat account in the pilot study, but we chose to release 10 articles regarding different themes.

After a month, the data collected from the WeChat official accounts platform showed that the average number of these articles that were actually read was 3.83. Family members in the intervention group were called to complete a questionnaire and make suggestions. The most appreciated feature within WeChat was convenience: family members considered it a convenient way to receive information.

We also conducted a semi-structured interview with 6 family members. Respondents (*n* = 6) reported that they regarded this WeChat public account as a tool to learn diabetes-related knowledge.*Though my mother has been diagnosed with diabetes for many years, I know little about this disease … and I am often confused with it. The articles from the WeChat public account I read are really helpful … I hope you can provide more information.* (A daughter)*Mother often told me not to worry about her … and I have little knowledge about her diabetes. Sometimes I feel frustrated because I don’t know how to help her. Information on the internet is too messy … I have little time to attend community health education lectures … The WeChat public account provides more convenience.* (A son)

Some respondents (*n* = 2) also reported that they wanted more detailed information about healthy eating.*Compared with other sorts of information, I want to have more understanding about how to eat. I think my father does well in other aspects, but not well in this.* (A daughter)*Eating is closely related to daily life; the article you put on WeChat is too brief. I only have a vague conception of what food diabetics should not eat.* (A wife)

However, there was a problem with the acquisition of information. Some respondents (*n* = 3) reported that they often neglected the articles.*And you know, I subscribe to many WeChat public accounts … .so I was unable to read every article from this public account.* (A daughter)

Based on the feedback from the pilot study, the intervention was revised. We added a WeChat personal account, named *Jiading Sugar Assistant*, as a supplement to deliver information to the participants individually. We also adjusted the content of the information, added more detailed information, and condensed knowledge.

### Outcome measures

The aim of this study is to improve clinical outcomes of patients with poorly controlled type 2 diabetes. HbA1c has been clinically used as a gold standard for assessing long-term glycemic control, reflecting over approximately 3-months blood glucose concentrations [40, 41]. Therefore, the primary outcome is the change in HbA1c of patients between at baseline and at the sixth month, and that between at baseline and the twelfth month.

Secondary outcome measures include changes in weight, height, waist circumference, hip circumference, blood pressure, BMI, blood glucose (fasting plasma glucose and 2 h post-load glucose), diabetes self-care activities, medication adherence, risk perception of diabetes, and family support. In addition, changes of family members’ diabetes-related knowledge and support to the patient are also assessed.

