#### Information delivery

To improve the accessibility of the intervention, the frequency and time of contacts must be considered. Too much information may bother participants. Thus, we decided to provide interventions twice a week. Although some studies have shown that WeChat users are more likely to receive push information from 8 a.m. to 11 a.m. and from 6 p.m. to 8 p.m. [38], there is no conclusion in terms of when is the most appropriate. Considering the working time of most people and the results of earlier studies [39], we will release the content at 5.00 p.m. to prompt the subscriber to accept the intervention. Due to the function of the WeChat application, the researcher can set the time to send the articles automatically. All information of this intervention can be conveyed by various methods such as text, images, videos, and audios.

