### Sample size

Sample size will be calculated based on the primary outcome, difference in mean HbA1c levels, assuming 80% power and a two-sided significance level of 0.05. The supposed effect size of HbA1c is 0.5%. We use the same standard deviation of HbA1C (1.2%) for calculations of the sample size, according to the data of 879 registered patients with HbA1C values more than 7.0% in the health information system in the two community health centers in central urban Jiading. Therefore, 92 participants are required in each group. Considering the possible lost follow-up rate of 20%, we will require 111 patients in each group for a total enrollment of 222 patient-family member dyads.

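### HbA1c change to month 6 and to month 12 are both primary and unranked, while the sample size covers one comparison and no primary contrast is named

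*Protocol article*

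**What the plan says.** - **Protocol article, Outcome measures:** the primary outcome is given as "the change in HbA1c of patients between at baseline and at the sixth month, and that between at baseline and the twelfth month". Two changes are listed and neither is put first.
- **Protocol article, Sample size:** the basis is stated as "Sample size will be calculated based on the primary outcome, difference in mean HbA1c levels". The error rate and power are set by "assuming 80% power and a two-sided significance level of 0.05". The assumed difference is 0.5 HbA1c percentage points. On variability: "We use the same standard deviation of HbA1C (1.2%) for calculations of the sample size". The result is "92 participants are required in each group", raised to 111 per group for loss to follow-up. One difference is sized, and the visit it refers to is not given.
- **Protocol article, Data analysis:** effectiveness is to be judged by group differences in the primary and secondary outcomes, using generalized linear mixed models because the data are longitudinal. No contrast from that model is identified as primary. A 0.05 significance level appears once, at the end of the paragraph on describing and comparing participants' characteristics.

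The article gives no order of testing, no split of the significance level, and no statement whether one or both changes must favour the intervention.

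**The concern.** The definition of the primary outcome and the sample size do not fit together. Two changes can show a benefit, but the error rate and power were set for one. The article leaves open what a positive trial is: an effect at month 6, at month 12, at either, at both, or on average over the two visits.

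At stake is how the main result may be read. If the two visits disagree, the conclusion could rest on whichever is favourable. Each way of settling the matter after the event has different error and power properties. If the two changes are read as separate tests at 0.05, the 5% and the 80% cannot both hold.

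**Working it through.** **Inputs.** From the Sample size section: difference 0.5, SD 1.2, two-sided 0.05, power 80%, 92 per group. Not in the document, so assumed: the correlation ρ between the month-6 and month-12 test statistics (0.5 to 0.9 is the main range, since both changes share the baseline value; 0 is shown as the limit for non-negative correlation), and the same effect and SD at both visits.

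**Step 1: reproduce the plan's figure.** The normal approximation for one comparison is n = 2 × [1.2 × (1.960 + 0.842) / 0.5]² = 90.4, so 91 per group. The exact t-test gives 92 per group, with power 80.3%. The stated 92 is therefore correct for one test.

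**Step 2: one test at n = 92.** The standard error is 1.2 × √(2/92) = 0.1769. The expected test statistic is 0.5 / 0.1769 = 2.826. Power by the normal approximation is Φ(2.826 − 1.960) = Φ(0.866) = 80.7%.

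**Step 3: two separate tests at 0.05.** Take (Z₆, Z₁₂) as bivariate normal with correlation ρ.
- Either suffices: family-wise error = 1 − P(|Z₆| ≤ 1.96 and |Z₁₂| ≤ 1.96) under no effect. At ρ = 0 this is 1 − 0.95² = 9.75%.
- Both required: power = Φ₂(0.866, 0.866; ρ). At ρ = 0 this is 0.807² = 65.1%. The type I error stays at or below 5%.

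**Step 4: one test from the mixed model.** Both forms below hold 5%.
- Joint 2-df test: noncentrality = 2 × 2.826² / (1 + ρ) = 15.97 / (1 + ρ).
- Average over the two visits: the SD becomes 1.2 × √((1 + ρ)/2), so the expected statistic is 2.826 / √((1 + ρ)/2).

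| ρ (assumed) | Either: family-wise error | Both: power, n = 92 | Joint 2-df: power | Averaged effect: power |
|---|---|---|---|---|
| 0.5 | 9.1% | 69.6% | 84% | 90% |
| 0.7 | 8.3% | 72.2% | 79% | 87% |
| 0.9 | 7.0% | 75.8% | 74% | 83% |

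**Step 5: what the alternatives would need.** For 80% power that both tests succeed, the number per group before dropout is 113 at ρ = 0.5, 109 at 0.7 and 102 at 0.9, against 92. With the level split to 0.025 per visit, power at each visit is 72.1% at n = 92, and 80% at each visit needs 110 per group. With one named contrast, or a fixed order of testing, 92 stays valid for the first test.

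**The case against.** **The mixed model may already supply a single test.** A joint group-by-visit test or an averaged effect would keep 5%. The averaged effect has 83% to 90% power at 92 per group over the assumed range, and the joint test 74% to 84%. This stands. A reader might infer that the stated error rate or the stated power must be wrong however the plan is read. The document does not support that, because either/both does not exhaust the options. What remains is that the article selects no such test and describes two separate changes.

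**The level of 0.05 is not assigned to each change.** Also true. The only 0.05 in the Data analysis section closes the paragraph on participants' characteristics. A full 0.05 for each visit is a natural reading, but it is an inference.

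**A testing rule may sit in an analysis plan that is not shown.** It may, and the absence of a rule from a condensed article would be weak ground by itself. The point rests on what the article does fix: two unranked primary changes beside a sample size for one. If an unseen plan required both, the article's 80% would not hold.

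**The size is illustrative.** The power figures need equal effects at both visits. They also carry over an SD taken from HbA1c values of registered patients, not from changes. The SD of change equals 1.2 only if the correlation between baseline and follow-up is 0.5.

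**A further inference to avoid** is that month 6 tests only half the intervention. About 105 articles at two a week would take 52.5 weeks, but only with one article per release. The Information delivery section says "we decided to provide interventions twice a week" and does not say how many articles each release carries. That argument is an assumption, and nothing here depends on it.

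**Conclusion.** The point holds as a mismatch within the protocol article: two unranked primary changes, a sample size for one comparison, and a model without a named primary contrast. Its size depends on the rule eventually used. With separate tests at 0.05, success on either gives a family-wise error of about 7% to 9% (ρ from 0.9 down to 0.5). Requiring both gives about 70% to 76% power at n = 92 (ρ from 0.5 up to 0.9, effect 0.5 and SD 1.2 at both visits). A single joint or averaged test would avoid the inflation. The document therefore leaves the success rule undefined; it does not show that 5% or 80% fails under every rule. The matter decides what counts as a positive trial and can be settled by wording.

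**What to change.** Name one primary contrast before any follow-up HbA1c exists. The Trial status section puts baseline assessment in January to February 2019 and the start of the intervention in March 2019, so on that timetable the choice can precede all outcome data.

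One suitable wording: the primary contrast is the between-group difference in HbA1c at 12 months, the end of planned follow-up, estimated from the planned mixed model and tested at two-sided 0.05. The 6-month difference is the first key secondary outcome, tested at 0.05 only if the 12-month test is significant. The fixed order holds the family-wise error for the two tests at 5%, and the stated calculation of 92 per group stays valid for the primary test under its own assumptions. The Sample size section should then name month 12.

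Other cures are acceptable if chosen in advance: a joint or averaged mixed-model contrast, the reverse order, a split level, or a rule that both must succeed. The last needs more patients (102 to 113 per group before dropout for ρ from 0.9 to 0.5). A split level needs 110 per group to keep 80% at each visit.

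Cost of the suggested wording: edits to the outcome, sample size and analysis sections, with no extra patients or visits. An effect seen only at 6 months could not be claimed as the primary result. Because the trial is registered, the registered primary outcome should be checked and may need updating.

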### Data collection

Data will be collected at baseline, 6 months, and 12 months for both patients and family members from the intervention group and the control group. For participants’ convenience, follow-up sessions will be scheduled based on the participants’ regular appointments, once every three months at the community health service stations.

Data collection will consist of two main parts: a questionnaire and biophysical data. Table 1 shows the measurement tools for patients’ data collection, the method and time points of data collection. The questionnaire data includes four main parts. The first part covers social demographics (e.g., sex, date of birth, education level, job, health insurance, marital status, annual income, family population composition, etc.). The second part concerns patients’ health status (e.g., time since diagnosis, therapeutic regimen, complications and co-morbidities, and hospital visit status due to diabetes). The third part is diabetes self-management behavior including activities of self-management [42] and adherence to medication [43]. The fourth part is psychosocial status, including risk perception [44], perceived family support [45], diabetes-related knowledge, and perceived benefits and barriers to diabetes self-care.

**Table 1 Tab1:** Patients’ variables and measurement tools used at each data collection time point

Variable	Measurement tools/questions	Baseline	6 mth	12 mth
Demographic measures	Sex, date of birth, ethnicity, education level, job, health insurance, marital status, annual income, family population composition	**√**		
Health status	Duration, therapeutic regimen, complications and co-morbidities, hospital visits due to diabetes	**√**		**√**
Behavior	Adherence to medication (Morisky Scale), activities of self-management (SDSCA)	**√**	**√**	**√**
Psychosocial variables	Risk Perception Survey–Diabetes Mellitus (RPS-DM), perceived family support (DFBC), diabetes-related knowledge, source of diabetes-related knowledge, perceived benefits and barriers to diabetes self-care	**√**	**√**	**√**
Biomedical measures	HbA1c, weight, height, waist circumference, hip circumference, blood pressure, BMI, blood glucose (fasting plasma glucose and 2 h post-load glucose)	**√**	**√**	**√**

The biophysical data, except for HbA1c, can be obtained from the medical record, including: weight, height, waist circumference, hip circumference, blood pressure, BMI, and blood glucose (fasting plasma glucose and 2 h post-load glucose). All these data will be collected as part of the family doctor team’s work. For the data on HbA1c, blood specimens will be collected from patients needing such testing by specifically trained staff according to standard procedures, then sent to the approved laboratory for analysis.

The questionnaire for collecting data from family members includes three main parts and will be administered by trained investigators. Table 2 shows that the first part covers social demographics (e.g., sex, age, ethnicity, religion, education level, job, health insurance, marital status, annual income, relationship with patients, etc.). The second part is health status (e.g., family history, chronic disease). The third part is family support and knowledge of diabetes.

**Table 2 Tab2:** Family members’ variables and measurement tools used at each data collection time point

Variable	Measurement tools/questions	Baseline	6 mth	12 mth
Demographic measures	Sex, age, ethnicity, education level, job, health insurance, marital status, annual income, relationship with patients	**√**		
Health status	Family history, chronic disease	**√**		
Family support and knowledge of diabetes	Family support (DFBC), diabetes-related knowledge, source of diabetes-related knowledge	**√**	**√**	**√**

The patients and their family members will be given linked ID numbers. The first three digits of the patient and his/her family member in the dyad will be the same, but the patients’ ID will end with the number “1” and family members’ ID will end with the number “2.”

### Data analysis

Descriptive statistics will be applied to describe the study population at baseline. We will analysis the categorical variables such as sex, job using frequency distribution description and centralized trend description. We will analysis the continuous variable using means±standard deviations. We will compare the difference of characteristics of participants (patients and family members) by t test or chi-square 2 test or non-parametric equivalent test. The *p* value 0.05 will be considered as the level of significance.

Effectiveness of the intervention will be measured by the differences primary outcome and secondary outcomes measures between study groups. The data about primary outcome and secondary outcomes are longitudinal data, thus we will use generalized linear mixed models. Potential confounders and effect modifiers (e.g., gender, age, and income) will be investigated.

Process data will consist of three parts, WeChat public account data, participation in diabetes self-management education, and an interview. The data from the WeChat public account mainly include: participants in the intervention who canceled their subscription, reading quantities of various sorts of articles (different information content and delivery methods), comments and questions. Patients’ participation in education will be recorded, and we will compare the difference between the intervention group and the control group.

Quantitative data will be analyzed with STATA using descriptive statistics. Semi-structured interviews of patients, family members, and staff of the family doctor teams will be analyzed with NVivo.

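### The primary outcome is change in HbA1c, but the trial is sized with the SD of single HbA1c levels and the plan does not say how baseline HbA1c enters the mixed model; a baseline-adjusted analysis would settle both at no cost

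*Protocol article*

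**What the plan says.** Three sections of the protocol article bear on this point.

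- **Outcome measures** puts the endpoint on the change scale: "the primary outcome is the change in HbA1c of patients between at baseline and at the sixth month". A second change, from baseline to month 12, is named in the same sentence.
- **Sample size** describes the same endpoint as a level: "Sample size will be calculated based on the primary outcome, difference in mean HbA1c levels". Power is set at 80% and alpha at 0.05, two-sided. The effect is given by "The supposed effect size of HbA1c is 0.5" percentage points. The spread is given by "We use the same standard deviation of HbA1C (1.2%) for calculations of the sample size". That SD comes from the centres' records of 879 patients whose HbA1c exceeded 7.0%. This leads to 92 patients per group before allowance for loss to follow-up.
- **Data analysis** gives the model in one sentence: "The data about primary outcome and secondary outcomes are longitudinal data, thus we will use generalized linear mixed models". It adds that possible confounders and effect modifiers will be looked at, with gender, age and income as examples. Baseline HbA1c is neither named nor ruled out.

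HbA1c is measured at baseline, 6 and 12 months (Data collection, Table 1). All baseline data are collected before randomisation, which is stratified by gender, duration of illness and age, but not by HbA1c (Randomization).

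**The concern.** One primary outcome is described in two ways. The SD of 1.2% describes how single HbA1c values vary between patients. The SD of a within-patient change is a different quantity and depends on the correlation between baseline and follow-up. The protocol article gives neither that correlation nor an SD of change, so a reader cannot tell whether the stated 80% power applies to the stated endpoint.

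The form of the mixed model decides whether this matters. A change endpoint measured at three visits is usually modelled with HbA1c at all three visits as the response and free group, visit and group-by-visit terms. With complete data, the group-by-visit coefficient for a follow-up visit is then exactly the difference between groups in mean change, so its precision is that of a change score. Baseline HbA1c as a covariate, or a common baseline mean for both groups, gives better precision. The plan does not choose between these forms.

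A low correlation cannot be ruled out. Entry requires HbA1c of 7.0% or more (Inclusion and exclusion criteria for patients), which narrows the baseline range and tends to lower the correlation.

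**Working it through.** **Inputs from the protocol article (Sample size):** difference 0.5, SD 1.2, two-sided alpha 0.05, power 80%, 92 per group. Allocation is 1:1 (Randomization).

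**Assumptions, not in the document:** the baseline-to-follow-up correlation r, shown from 0.3 to 0.7, and an SD of 1.2 at both baseline and follow-up.

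**Step 1. Reproduce the plan's figure.** The normal formula gives n = 2 × (1.2 × (1.960 + 0.842) / 0.5)² = 90.4, so 91 per group. The t-based calculation gives 91.4, so 92, as stated. Power with 92 per group is 80.3% (t-based). The figure is correct for comparing follow-up levels with an SD of 1.2.

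**Step 2. SD on each analysis scale.**

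- Unadjusted change: SD = 1.2 × √(2(1 − r)). This equals 1.2 only when 2(1 − r) = 1, that is r = 0.5.
- Adjusted for baseline: SD = 1.2 × √(1 − r²). This never exceeds 1.2.

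Example at r = 0.3: change 1.2 × √1.4 = 1.42; adjusted 1.2 × √0.91 = 1.14.

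**Step 3. Power with 92 per group and a difference of 0.5 (two-sample t).**

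| Assumed r | SD of change | Power, change | SD adjusted | Power, adjusted |
|---|---|---|---|---|
| 0.3 | 1.42 | 66% | 1.14 | 84% |
| 0.4 | 1.31 | 73% | 1.10 | 87% |
| 0.5 | 1.20 | 80% | 1.04 | 90% |
| 0.6 | 1.07 | 88% | 0.96 | 94% |
| 0.7 | 0.93 | 95% | 0.86 | 98% |

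**Step 4. The same in patients.** At r = 0.3, 80% power needs 128 per group for an unadjusted change and 84 per group with baseline adjustment. The plan has 92.

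**Step 5. What the figures do not cover.** They describe a comparison at one follow-up visit. They are not a simulation of a model that uses both visits. If the SDs at baseline and follow-up differ, the break-even correlation moves away from 0.5, and the adjusted SD becomes the follow-up SD × √(1 − r²).

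**The case against.** The strongest reply is that the Data analysis section states nothing wrong. A reader might infer that the analysis will not be adjusted for baseline HbA1c, since only gender, age and income are mentioned. The text does not support that: those three are given as examples, and baseline HbA1c is not excluded. The planned mixed model may already use the baseline as a repeated response. With a common baseline mean it would be about as precise as baseline adjustment. Model terms are also commonly left to a statistical analysis plan or full protocol, which are not shown. All of this stands, so the missing model detail is not in itself an error.

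It is also right that randomisation makes the expected group difference in change equal to the expected difference in follow-up levels. Both sections therefore target the same 0.5% effect, and only the scale of the SD is open. A reader might infer that the trial is underpowered. That does not follow: no r is given, and at r = 0.6 or 0.7 even an unadjusted change score exceeds 80% power.

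The reply does not remove the difference between Outcome measures and Sample size. Those are two stated descriptions of one primary outcome, not detail deferred elsewhere. Nor does it help if the usual free group-by-visit model is the one fitted.

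**Conclusion.** The point holds in a conditional form. The endpoint is a change, the sample size rests on the SD of levels, and nothing links the two. For an unadjusted change comparison, the stated 80% power requires r of about 0.5 or more: power is about 66% at r = 0.3 and 95% at r = 0.7. With baseline adjustment, 92 per group keeps power at 80% or slightly more even at r = 0, and reaches 84% to 98% over r = 0.3 to 0.7. These figures assume an SD of 1.2 at both times; r is assumed throughout.

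The documents do not show that precision will be lost, only that the plan leaves this open. It is still worth acting on. Conditioning on a measurement planned for every patient makes the stated 92 per group adequate whatever the correlation, provided the follow-up SD is also about 1.2. It also accounts for chance imbalance in HbA1c, on which randomisation is not stratified.

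**What to change.** 1. In Data analysis, specify the primary analysis as a linear mixed model for HbA1c at 6 and 12 months with group, visit, group-by-visit, baseline HbA1c and baseline-by-visit terms. A constrained longitudinal model with a common baseline mean for both groups is an acceptable alternative.
2. Report the adjusted group difference at each of the two visits named in Outcome measures.
3. Reconcile Sample size with Outcome measures by stating that the 0.5% effect and the 92 per group refer to this baseline-adjusted difference. Add that an SD of 1.2 is adequate or conservative for it if the follow-up SD is also about 1.2.

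The cost is wording only. Baseline HbA1c is already scheduled for every patient before randomisation, and the 92 per group need not change on this account.
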